**Home care practices**	

Clean delivery practices	For home births only: % of births for which attendant washed their hands with soap % of births for which attendant/mother had a sheet % of births for which attendant had new or boiled blade % of births for which attendant boiled thread % of births for which attendant washed their hands % of births for which attendant put nothing/antiseptic on cord

Immediate and exclusive breastfeeding	% of liveborn infants breastfed within first hour % of liveborn infants exclusively breastfed for first six weeks

Thermal care	% of liveborn infants wrapped within first hour after birth % of liveborn infants wiped within first hour after birth % of liveborn infants not bathed in first 24 hours after birth

Skin-to-skin/kangaroo care	% of liveborn infants given kangaroo (skin to skin care) within the first hour after birth

**Interaction with other interventions**	

Home visits & JSY	% mothers who received home visits on the 1^st ^day of life % mothers who received home visits on 1^st^, 3^rd ^and 7^th ^day of life % mothers who had an institutional delivery assisted by the Janani Suraksha Yojana scheme

### Selection of clusters and unit of randomisation

The trial area covers a population of approximately 158,053 (based on 2001 Indian Census data) in three districts of Jharkhand (Ranchi, Khunti and Godda) and two districts of Orissa (Mayurbhanj and Rayagada). The location of study areas is shown in Figure 1 and district characteristics in Table 2. The unit of randomisation is a rural geographic cluster of approximately 5000 population. Within each district, the intervention team mapped villages and formed 6 clusters constituted of 5-8 villages and their neighbouring hamlets, with at least 10 active ASHAs per cluster. Within each district, 6 clusters were randomly allocated to receive the community intervention or to the control group, as described in Figure 2. Intervention and control clusters are separated either by natural boundaries (rivers or hills), or by 'buffer villages' not enrolled in the trial.

**Figure 1 F1:**
[figure not shown]
**Study area**.

**Table 2 T2:** Study area characteristics

District	Population*	ASHAs (n)	Villages (n)
Ranchi	31,135	104	35
Godda	29,097	42	41
Rayagada	34,144	56	99
Mayurbhanj	31,913	50	52
Khunti	31,764	66	71

Total	158,053	318	298

* 2009 projection from 2001 Indian Census

**Figure 2 F2:**
[figure not shown]
**Trial design**.

### Setting

The study takes place in two districts of Orissa and three districts of Jharkhand, two states of eastern India. The five districts are largely rural and have a high proportion of *adivasi *people. The main tribal groups in the trial area are the Ho, Munda, Oraon, Santhal, Binjhiya, Paharia, Bhumij, Bhatudi, Bhuyian, Gond, Mankidia and Kondh. In previously published research carried out in other rural tribal areas of these states, [22] we found a neonatal mortality rate of 58 per 1000 livebirths and a maternal mortality ratio of 510 per 100 000 livebirths. Around 35% of mothers had three or more antenatal check-ups and only 17% delivered in a health facility. In December 2010, the recruitment of ASHAs had been completed in Jharkhand and Orissa but their training in home-based newborn care had not begun. JSY was operating in both states but had higher coverage in Orissa [13]. The trial is being implemented by Ekjut, an NGO that has been working in Jharkhand and Orissa since 2003, in collaboration with the Centre for International Health and Development at University College London (UK).

### Target group and eligibility criteria

The target population will be rural, mainly tribal communities with poor access to health services. The target group for the women's group intervention is women of childbearing age between the ages of 15 and 49 years, and particularly pregnant mothers. However the groups are open to all community members, including adolescent girls, older women and men. Community health workers may also participate in group discussions. Participants in the trial will be all women who have given birth in the study area between 1^st ^September 2009 and 31^st ^of August 2010 for the baseline period, and between 01^st ^of September 2010 and 31^st ^December 2012 for the trial period, and who have agreed to take part in the study when approached by an interviewer around six weeks after delivery. Excluded are women who decline to be interviewed or have migrated out of the study clusters, and, for secondary outcomes (care-seeking and home care practices), women who gave birth in the study area but who cannot be traced after 9 months. During an earlier trial, 1.3% of births detected by a similar surveillance system to the one used in this study (255 out of 19068) were to mothers who migrated in or out of the study clusters, and we were not able to obtain background socio-economic data on these migrants. The intention to treat population (for the primary outcome) will therefore be all mothers who reside in the study clusters and have given birth in the study area in the last 24 months of the intervention and did not migrate out of the study clusters. Participation in intervention activities will be voluntary and women are free to join or leave a group at any time.

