**Methods/design:**

The study is a cluster-randomised controlled trial and will be implemented in five districts, three in Jharkhand and two in Orissa. The unit of randomisation is a rural cluster of approximately 5000 population. We identified villages within rural, tribal areas of five districts, approached them for participation in the study and enrolled them into 30 clusters, with approximately 10 ASHAs per cluster. Within each district, 6 clusters were randomly allocated to receive the community intervention or to the control group, resulting in 15 intervention and 15 control clusters. Randomisation was carried out in the presence of local stakeholders who selected the cluster numbers and allocated them to intervention or control using a pre-generated random number sequence. The intervention is a participatory learning and action cycle where ASHAs support community women's groups through a four-phase process in which they identify and prioritise local maternal and newborn health problems, implement strategies to address these and evaluate the result. The cycle is designed to fit with the ASHAs' mandate to mobilise communities for health and to complement their other tasks, including increasing institutional delivery rates and providing home visits to mothers and newborns. The trial's primary endpoint is neonatal mortality during 24 months of intervention. Additional endpoints include home care practices and health care-seeking in the antenatal, delivery and postnatal period. The impact of the intervention will be measured through a prospective surveillance system implemented by the project team, through which mothers will be interviewed around six weeks after delivery. Cost data and qualitative data are collected for cost-effectiveness and process evaluations.

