##### Surveillance

A monitoring team independent from the intervention team was established to collect information on births and deaths to women of reproductive age and on events during the antenatal, delivery and postnatal periods through a surveillance system adapted from a previous study, covering a total population of around 158,053 [31] and described in Figure 3. One key informant (a community member) reports all births and deaths to women of reproductive age to an interviewer. The informant is visited on a monthly basis by an interviewer from the surveillance team. The interviewer checks the report, pays the informant an incentive of Rs30 for an identification and another Rs 50 for conducting an interview with the identified mother around six weeks after the delivery. The collected questionnaires are examined by District Monitoring Coordinators with guidance from District Managers. Completed questionnaires are then entered into a database designed in Microsoft Access. Baseline data on birth outcomes were collected for a full year from 1^st ^September 2009 to 31^st ^August 2010.

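### The population called intention to treat for the primary outcome depends on events after randomisation, and its consent and place-of-birth conditions are not settled

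*Protocol article*

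**What the plan says.** All the relevant text is in the protocol article, mostly under Target group and eligibility criteria.

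- **Primary population.** "The intention to treat population (for the primary outcome) will therefore be all mothers who reside in the study clusters" and who "have given birth in the study area in the last 24 months of the intervention and did not migrate out of the study clusters". Residence is tied to the clusters and birth to the study area. The second term is not defined.
- **Participants.** Women who gave birth in the study area and "who have agreed to take part in the study when approached by an interviewer around six weeks after delivery".
- **Exclusions.** "Excluded are women who decline to be interviewed or have migrated out of the study clusters". A further exclusion, for women who cannot be traced after nine months, is confined to the secondary outcomes. The exclusions for declining and moving out carry no such limit.
- **Reason.** In an earlier trial 1.3% of detected births were to mothers who moved in or out, and "we were not able to obtain background socio-economic data on these migrants". The definition of the primary population follows from this by a 'therefore'.
- **Analysis.** Data monitoring, masking and analysis plan promises intention-to-treat analyses of individual-level data and says that participants cannot be blinded.
- **Data capture.** Under Surveillance, a key informant "reports all births and deaths to women of reproductive age to an interviewer".

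**The concern.** An intention-to-treat comparison keeps everyone in the arm to which their cluster was allocated, whatever happens later. Here three filters act after allocation.

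1. **Out-migration.** These births can be detected by surveillance. An unadjusted neonatal mortality rate needs livebirth and survival to 28 days, not socio-economic covariates. Missing covariates can justify leaving a birth out of an adjusted model, but not out of the crude analysis.
2. **Place of birth.** If the condition means what it literally says, residents who deliver elsewhere are lost. The intervention could plausibly affect this. Its meetings cover care-seeking and emergency preparedness (Women's groups; Table 3), and the cycle is meant to complement ASHA tasks "including increasing institutional delivery rates and providing home visits to mothers and newborns".
3. **Declining at about six weeks.** The decision is made after the neonatal period, by women who are not blinded. The participant definition and the exclusions remove decliners, while the sentence on the primary population is silent. The text therefore does not settle whether their births count.

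At stake is the denominator and numerator of the primary endpoint. If the excluded births differ in risk between arms, or differ in number between arms and in risk from the rest, the mortality ratio is biased and adjustment for clustering does not help.

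**Working it through.** **Inputs from the protocol.** Control rate p0 = 0.055, intervention rate p1 = 0.0385, n = 200 livebirths per cluster (100 a year for 2 years), c = 15 clusters per arm, k = 0.1 (Sample size); 255 of 19068 births to migrants (Target group and eligibility criteria). **Assumptions.** Two-sided alpha of 0.05, and every mortality rate among excluded births and every share excluded other than migration.

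**1. The plan's own power.** Hayes and Bennett, with v = [p0(1−p0) + p1(1−p1)]/n + k²(p0² + p1²):

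- v = 0.088993/200 + 0.01 × 0.004507 = 0.000490
- Unmatched: z = √(14 × 0.0165²/0.000490) − 1.96 = 0.829, power 79.6%
- Matched: 13 in place of 14 gives z = 0.727, power 76.7%

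The stated range is 76.6% to 79.6%, so the plan's figure reproduces.

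**2. Power after losing migrants.** 255/19068 = 1.34%, or about 40 of 3000 births per arm. Power falls to 79.2% (unmatched) or 76.1% (matched). The issue is bias, not power.

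**3. Bias formula.** If a share e of births with mortality m is dropped from an arm with true rate p, the observed rate is (p − e·m)/(1 − e). The true rate is set at 55 per 1000 in both arms, so an unbiased risk ratio is 1.

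**4. Migration, 1.3% dropped in each arm**

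| Mortality per 1000 among dropped births (intervention / control) | Observed rates | Risk ratio |
|---|---|---|
| 55 / 55 | 55.0 / 55.0 | 1.000 |
| 110 / 55 | 54.3 / 55.0 | 0.987 |
| 200 / 55 | 53.1 / 55.0 | 0.965 |
| 200 / 200 | 53.1 / 53.1 | 1.000 |
| 55 / 200 | 55.0 / 53.1 | 1.036 |

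Third row: (0.055 − 0.013 × 0.2)/0.987 = 0.0531. If the true ratio were 0.70, the same pattern would give (0.0385 − 0.0026)/0.987 = 0.0364, a ratio of 0.66. As an extreme bound, if every dropped intervention infant had died and no control birth was dropped, (0.055 − 0.01337)/0.98663 = 0.0422, a ratio of 0.77.

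**5. Place of birth, if births outside the area really were dropped**

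| Share dropped (intervention / control) | m = 27.5 per 1000 | m = 110 | m = 165 |
|---|---|---|---|
| 5% / 2% | 1.016 | 0.967 | 0.933 |
| 10% / 5% | 1.028 | 0.938 | 0.869 |

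Example: with 10% against 5% and m = 165, (0.055 − 0.0165)/0.90 = 0.0428 and (0.055 − 0.00825)/0.95 = 0.0492, a ratio of 0.869.

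**The case against.** The strongest reply is that the place-of-birth filter is probably not intended. Table 1 counts births in public or private facilities and deliveries assisted by the JSY scheme, and Sub-analyses compares institutional delivery between areas with and without the intervention. These endpoints make little sense if births outside the enrolled villages are discarded. Detection is also community-based. This stands: the phrase is ambiguous and needs a definition, but the exclusion is not established.

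The migration exclusion is disclosed with its reason and expected size, and that size is small. Detecting a birth also does not establish 28-day survival for a family that has left. Both points stand. They limit the effect, but they do not make the population intention to treat.

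A reader might infer more than the text supports:

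- **That the bias favours the intervention.** The protocol gives no arm-specific figures for migration, refusal or outside delivery. The ratio falls on either side of 1 depending on assumptions. ASHAs work in all clusters, so their mandate on institutional delivery is not itself a difference between arms.
- **That the ratio could fall to 0.84.** This comes from dropping 17% of control and 25% of intervention births at 110 per 1000: 36.7/43.7 = 0.84. It assumes that every facility birth is excluded. The 17% comes from earlier research in other areas (Setting), and the 25% and 110 are assumed.
- **That the mother must be alive, so maternal mortality cannot be counted.** No such condition is stated. Key informants report women's deaths, Individual consent refers to birth or death identifications, and maternal mortality is listed in Table 1. Who answers for a mother who has died is detail that an article may leave to the full protocol.

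**Conclusion.** The point holds at moderate severity. The population labelled intention to treat is conditioned on not moving out and, read literally, on delivering in an undefined study area. Whether decliners' births count towards neonatal mortality is contradictory or at least unresolved. The stated reason supports exclusion from covariate-adjusted models only.

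The direction of any bias is unknown. At the documented 1.3%, which combines in- and out-migrants and comes from an earlier trial, the risk ratio under no effect stays within about 0.965 to 1.036 even with 200 against 55 deaths per 1000 among those dropped. A range of about 0.87 to 1.03 needs two further assumptions: that outside births really are excluded, and that the shares are 5% and 10% with half to three times the average risk. The refusal rate is not given, so its effect cannot be sized. Equal exclusions at equal risk leave the ratio unchanged.

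**What to change.** - Define the primary population as all livebirths in the 24-month window to women resident in a study cluster, with residence fixed before the outcome is known (for example, at delivery), wherever the birth took place, analysed in the cluster of residence.
- Include mothers who later move out whenever 28-day survival is known.
- Define the study area, or remove it from the population sentence.
- Reconcile the consent wording. Either state that decliners' births count for neonatal mortality where surveillance gives birth and vital status and ethical approval allows, or call the population modified intention to treat.
- Limit exclusion for missing socio-economic data to covariate-adjusted analyses.
- Report exclusions by arm and reason.

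The cost is mainly wording, since surveillance is already meant to detect these births; using decliners' data would also need ethical agreement. The downside is small: fewer covariates and some unknown vital status among the added births. The change should be made before the analysts are unblinded.

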### Randomisation and allocation

The randomisation was carried out as follows: in each district, we invited stakeholders from each cluster, including Village Health Committee members and staff from other NGOs to a meeting. We allocated a number to each cluster, wrote these numbers on small plastic balls and placed the balls within a dark bag. The intervention team reminded stakeholders about the aim and length of the intervention and about the purpose of the randomization process. We asked each of the participants to draw one ball from the bag and read the cluster number out until all balls had been picked. The numbers were then written on a sheet of paper in the order of selection. Finally we placed twenty pieces of paper numbered 1 to 20 - each corresponding to a unique allocation sequence generated by CP in Excel - in the dark bag and asked a participant to select a paper and read out the number. The corresponding sequence was then used to publicly allocate each cluster to one of two groups to ensure transparency among the stakeholders and also to avoid conflict as only intervention area ASHAs would be entitled to incentives.

#### The interventions

##### Women's groups

The intervention is a participatory learning and action cycle of 20 meetings, during which women's groups open to other community members identify and prioritise maternal and newborn health problems in their area, identify strategies to address these, implement these strategies and evaluate the entire process. This cycle was adapted from an earlier intervention tested during the Ekjut trial and in other settings [27,28]. Specific adaptations based on lessons from the Ekjut trial included a minimum recruitment of pregnant women into groups and an emphasis on care for newborns during winter, as a strong increase in neonatal deaths was observed in the study areas during this season. The team also prioritized materials to be used (e.g. picture cards) by selecting the most important maternal and newborn problems with ASHAs. The cycle consisted of fortnightly meetings for the first four months (Phase 1 and Phase 2), following by monthly meetings after this, as described in Table 3. In the first phase, consisting of three meetings, the ASHA will introduce the project, then help the group identify and prioritise local maternal and newborn health problems. In the second phase, consisting of four meetings, groups discuss causes and solutions to prioritized problems through participatory games and using picture cards, then identify and prioritise strategies for addressing the problems. At the end of this phase the groups prepare to hold a community meeting in which they share their thoughts, problems and strategies with other community members, including men, traditional birth attendants, mothers-in-law and Community Health Workers. In phase three, the groups implement their strategies and carry out practical role-plays focusing on care-seeking and emergencies. Finally, in phase four the groups evaluate each of the phases and progress on their prioritized strategies. The intervention is expected to run for 24 months (20 meetings, two community meetings and two additional months to make up for any cancellations of meetings).

**Table 3 T3:** Intervention meeting plan

ASHA TRAINING 1		
**Phase I: **Problems	Meeting 1	Introduction to the project
	Meeting 2	Identifying & prioritizing maternal problems in the community
	Meeting 3	Identifying & prioritizing neonatal problems in the community

**ASHA TRAINING 2**		

**Phase II:** Strategies	Meeting 4	Thermal care for newborns (story on preventing winter deaths)
	Meeting 5	Understanding causes and solutions for prioritized problems (story focusing on causes, effects and management)
	Meeting 6	Identifying and prioritising strategies for implementation
	Meeting 7	Choosing a method & preparing for sharing at the community meeting
	Meeting 8	Preparing for a community meeting

**COMMUNITY MEETING 1 AND ASHA TRAINING 3**		

**Phase III:** Implementation	Meeting 9	Assigning responsibilities for the implementation of strategies
	Meeting 10	Birth preparedness - Hygienic practices - Essential Newborn Care - Management of twins and low birth weight babies (demonstration)
	Meeting 11	Understanding & implementing home care strategies using picture cards
	Meeting 12	Understanding & implementing preventive strategies using picture cards
	Meeting 13	Understanding & implementing strategies for newborn emergency problems using picture cards
	**ASHA TRAINING 4**	
	Meeting 14	Accessing appropriate care (game)
	Meeting 15	Emergency preparedness for maternal and neonatal problems (role-play)
	Meeting 16	Preventing maternal deaths through campaigning against the first delay
	Meeting 17	Learning about strategies implemented by other groups
	Meeting 18	Preparation for community meeting
		**COMMUNITY MEETING 2**
	**ASHA TRAINING 5**	

**Phase IV:**	Meeting 19	Phase-wise evaluation
Evaluation	Meeting 20	Evaluation of women's group activities

##### ASHA selection, training and incentivisation

In each district we approached district-level ASHA coordinators and Village Health Committees (VHCs), explained the women's group intervention and asked VHCs to identify suitable ASHAs to facilitate the groups. These ASHAs had to be functional according to government criteria: they needed to have undergone at least three training sessions and be village-based. We identified problems that could arise whilst working with ASHAs during the course of the intervention and agreed on strategies to address these. In order to assist the ASHAs, we appointed a co-facilitator who was given an incentive of Rs 50 per meeting to help with record keeping. This co-facilitator was not given training to conduct meetings, and ASHAs were left in charge of facilitation. Should an ASHA not be accepted by her village, we agreed that the district-based intervention team would seek to help her, and, if unsuccessful, ask the co-facilitator to conduct meetings after training. In the event that an ASHA should drop out of the intervention permanently the VHC and women's group would decide whether a new ASHA should be trained, or whether a co-facilitator should take over and be paid the full incentive. The intervention team designed four training sessions for selected ASHAs, one for each phase of the intervention. One cluster coordinator employed by Ekjut is posted in each district. ASHAs are given an incentive of Rs100 per day as in government trainings (US$2) and Rs200 per meeting. A total of 149 ASHAs were selected to implement the intervention.

